### Health economic evaluation

A health economic analysis from the perspective of the UK NHS and Personal Social Services will be conducted alongside the trial. A detailed health economic analysis plan (HEAP) will be produced alongside the SAP, including strategies for dealing with missing data. We will use routine data at 24 months to capture a detailed profile of healthcare resource use (e.g. unscheduled care, prescriptions) in both implementation and control practices. Resources associated with implementing the IMP^2^ART strategy will be determined from trial data. Resource use will be valued in £ sterling using published unit costs [70].

Using the primary outcome, a cost-effectiveness analysis will be undertaken with appropriate, discounting of costs and benefits (3.5%). We will undertake deterministic sensitivity analyses to assess the impact of parameter changes on our base-case incremental cost-effectiveness ratio (ICER). In order to provide a comprehensive picture of the health economic findings, costs will be tabulated for all other outcomes, as part of a cost-consequences approach [71].

We will undertake a cost-utility analysis to estimate the incremental cost per quality-adjusted life year (QALY) of IMP^2^ART compared to control at 24 months. A decision analytical model will be constructed, informed by structured literature searches and in consultation with the IMP^2^ART team. We will derive health utilities from the literature. All model inputs and assumptions will be agreed with the IMP^2^ART experts for the base-case analysis and inform the parameters and assumptions to be tested in sensitivity/scenario analysis.

A cost-utility analysis will examine the incremental cost/QALY. QALY gains or losses will also be used in a net–benefit analysis based on accepted NICE ‘value for money’ thresholds. Deterministic sensitivity analysis will assess the impact of parameter variation on the baseline estimates. Probabilistic sensitivity analysis will investigate the joint uncertainty in parameter values, and cost-effectiveness acceptability curves will illustrate uncertainty surrounding the estimates of cost-effectiveness and probability (in % likelihood) of the intervention being cost-effective against society’s willingness to pay, using NICE thresholds [72]. We will explore longer-term cost-effectiveness, using estimates derived from the trial and information from literature sources relating to longer-term costs and effects (QALYs) to arrive at plausible long-term estimates of cost-effectiveness.

### Process evaluation

The trial will include a nested process evaluation to understand the national/local practice context and changes over time, assess fidelity and/or adaptation of the implementation strategy, assess receipt and response to the implementation strategy (i.e. how much of the different components was actually received and taken up by practice staff), explore reach and potential for scaling-up and explore sustainability to inform if/how the intervention is embedded. Using established case study methodology [73], we will conduct in-depth case studies in up to four implementation practices to understand their process of implementing IMP^2^ART. The case studies will involve: interviews (*n*≈12/case study) with individuals who deliver supported self-management in the practice; observation of activities (*n*≈10–20 h/case study), e.g. training sessions, practice meetings; documentary analysis (»40/case), e.g. anonymised notes and plans, meeting minutes; audio-recording asthma clinics (*n* = 3/case study) to assess delivery of supported self-management within routine reviews.

Additionally, facilitator log books will be completed throughout the trial, and an exit survey for all practices will be conducted. Up to 12 interviews with key informants (e.g. practice nurses, GPs, practice managers) will be undertaken in non-case study practices to understand specific aspects of implementation of supported self-management in practices, responses to IMP^2^ART strategies, and to explore the transferability of preliminary case study findings. Additional focussed interviews (*n*≈10) will be conducted with national/regional opinion leaders, healthcare managers and policymakers, to explore policy perspectives and/or generalisability of emerging themes. We will interview all facilitators (*n*≈4) about their experience of facilitating the delivery of IMP^2^ART.

Implementation fidelity with be assessed and will include both adoption and adaptation of the implementation strategy. We will follow the National Institutes of Health Behaviour Change Consortium’s fidelity framework [74] to consider the five aspects of fidelity (study design, training providers, treatment delivery, treatment receipt, treatment enactment). This will include the following: assessment of facilitator training and facilitator delivery of IMP^2^ART (video-recording of the IMP^2^ART workshop), treatment receipt will be monitored by uptake of skills by practices and use of implementation strategies. We will follow FRAME-IS to report adaptations to the implementation strategy [75].

A mixed methods analysis will be conducted for the process evaluation to understand the extent to which delivery or response to IMP^2^ART strategies or the national/local context influenced the outcomes achieved. Qualitative and quantitative analysis will be undertaken concurrently with findings from each used to inform the interpretation of the other.

### Impact of the COVID-19 pandemic on outcomes

In addition to affecting trial timelines and requiring intervention modifications the pandemic also had an impact on trial outcomes and consequently the statistical analysis. Restrictions on movement and interaction with people outside of one’s household were imposed leading to reduced viral spread and reduced access to healthcare (the public were encouraged to access healthcare only when absolutely necessary) [66, 67]. There is also evidence [66] of increased demand for preventer medication at the onset of the lockdown (March 2020) though whether this represents improved adherence to medication or stockpiling is unclear. Our analysis of a large dataset provided by OPC research database confirmed marked changes in primary and secondary outcomes in the first year of the pandemic compared to the prior year.

The original intention was that statistical analysis models would adjust for baseline, that is, the 12 months prior to randomisation. The main analysis of outcomes has now been changed to models not adjusting for baseline as the effect of the pandemic on baseline outcomes will differ for clusters. For practices recruited earlier, the baseline period will overlap with the pandemic and associated restrictions to a large extent whilst for practices recruited later there were fewer, if any, restrictions (note that there were also regional variations in restrictions). Consideration was given to using the 12-month period prior to the pandemic as the baseline. This was also rejected as (a) the time period between baseline and follow-up would vary for clusters and (b) for participants to be included in the study data they would have to be a registered patient with that practice at all three time points, and this longer overall time period would have reduced the sample size. However, data will be extracted from the 12 months before the start of the pandemic until the 24 months follow-up ends and three sensitivity analyses will be conducted—a model adjusting for baseline at the individual level, a model adjusting for baseline at the individual level using the 12 months before the pandemic as the baseline period, and a repeated measures model using baseline, 12-months and 24-month follow-up.

In addition, the pandemic also led to more GP consultations being conducted remotely (telephone or video). New codes for this were introduced which may have resulted in changes to routine data coding practices. Therefore, the code lists defining the primary clinical outcome and secondary outcome which were derived in an early phase of the programme needed to be updated.

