### Clinically eligible patient population

This is a practice-level intervention and we are not recruiting individual patients to the trial. Our patient population is all people who are eligible clinically to be offered supported asthma self-management by the practice. In line with national/international guideline recommendations, this is all patients with a diagnosis of ‘active’ asthma [3–5, 47]. The only exclusions (which we will apply in defining our patient populations from routine data) are:Under 5 years of age. Standard approaches to asthma self-management are ineffective in this age group [3].Under the care of a severe/difficult asthma clinic [3–5], though supporting their specialist action plan is appropriate.Significant co-morbid chronic obstructive pulmonary disease [48], as this requires a COPD action plan.Identified by the practice as being clinically unsuitable (e.g. severe cognitive impairment, on the palliative care register (a list held by the practice of those under their care who may be approaching end of life)).

Our primary health outcome (unscheduled care) will be assessed on routine data from the whole eligible population as defined above (excluding any patient whose EHR is coded as not wanting their data used for any purpose other than their care) and who have been on the ‘active asthma’ register of the practice throughout the 3-year data collection period (1-year pre-trial and 2-years during the trial).

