### Statistical analysis

Analysis will be on data at 12 months (implementation/process outcomes) and 24 months (health outcomes) follow-up. Individuals will be included in the analysis only if they were registered in a practice at baseline, 12 months and 24 months follow-up. Practices will be analysed in the group to which they were allocated regardless of compliance (intention-to-treat). The target of estimation is the average treatment effect across participants in terms of the primary clinical as well as primary implementation outcome. An unweighted independence estimating equation analysis on participant-level data will be used to estimate the participant-average difference in proportions between groups. This model employs an independence working correlation structure in conjunction with robust standard errors to account for clustering. Secondary outcomes will be analysed using the same or a similar model appropriate for the respective variable type. The models will include fixed effects for stratification variables and may incorporate additional individual-level covariates as fixed effects (covariates are limited as we are taking them from routine data). A fully pre-specified model will be provided in the statistical analysis plan (SAP). Treatment effect estimates, with associated confidence intervals and *p*-values, and ICCs will be reported for each outcome.

The primary clinical outcome as well as the secondary outcomes of unscheduled care (12 months), asthma attacks and prescribing outcomes will, by definition, not have any missing data as the absence of a code describing an event or prescription is defined as the binary variable value ‘no’. Patterns and amount of missing data for questionnaire outcomes and other routine data variables will be explored, and a suitable multiple imputation method used. The strategy for dealing with missing values will be articulated in detail in the SAP which will be prepared by the Pragmatic Clinical Trials Unit (PCTU) statisticians in consultation with other blinded research team members. Allocation codes will not be released to the statisticians before the SAP is signed off and made publicly available.

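### Baseline adjustment is dropped from the main analysis for a reason that does not affect validity; restoring it, with the practice's baseline proportion, could gain precision at almost no cost

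*Protocol article*

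**What the plan says.** The section Impact of the COVID-19 pandemic on outcomes records a change of plan: "The original intention was that statistical analysis models would adjust for baseline, that is, the 12 months prior to randomisation". It continues: "The main analysis of outcomes has now been changed to models not adjusting for baseline", and gives the reason "as the effect of the pandemic on baseline outcomes will differ for clusters". Practices recruited early have a baseline year that largely overlaps the restrictions, later ones have little or no overlap, and restrictions varied by region.

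A pre-pandemic baseline year was considered and rejected, because its distance from follow-up would vary between practices and the longer registration requirement would shrink the sample. Even so, "data will be extracted from the 12 months before the start of the pandemic until the 24 months follow-up ends". The same section adds that "three sensitivity analyses will be conducted": one adjusting at the individual level for the pre-randomisation year, one adjusting at the individual level for the pre-pandemic year, and one repeated measures model.

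The Statistical analysis section plans an unweighted independence estimating equation with robust standard errors for the participant-average difference in proportions. On covariates it says: "The models will include fixed effects for stratification variables and may incorporate additional individual-level covariates as fixed effects". Under Clinically eligible patient population, analysed patients must have been on the practice's active asthma register "throughout the 3-year data collection period (1-year pre-trial and 2-years during the trial").

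**The concern.** The reason given would matter if adjusting for a disturbed baseline could distort the comparison between arms. It cannot. Each patient's baseline value is fixed before the practice is allocated. Randomisation is 1:1 by practice, so recruitment date, region and pandemic exposure differ between arms only by chance. The Strengths and limitations section itself expects the pandemic to bear on both arms alike. Uneven disturbance makes baseline a poorer predictor in some practices and so reduces what adjustment can gain.

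What may be lost is precision. In a cluster trial of this shape, the uncertainty of the treatment effect comes almost wholly from differences between practices, and a practice's earlier level of unscheduled care is a natural covariate for explaining them. The two objections to the pre-pandemic year do not carry over to the 12 months before randomisation. That year lies at a fixed distance from follow-up, and membership of the register during it is already a condition of entering the analysis.

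**Working it through.** **Inputs.** From Sample size calculations: ICC 0.07; mean cluster size m = 200; coefficient of variation CV = 0.8; 70 practices per arm after losses; 25.8% v 18.8%; stated power 94.7%. From Statistical analysis: unweighted independence estimator. Not in the documents, hence assumed: the correlation r between a practice's observed baseline proportion and its second-year proportion (0 to 0.7), and a within-practice individual correlation of 0.3.

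**The plan's own figure.** With equal clusters the design effect is 1 + 199 × 0.07 = 14.93, so the effective number per arm is 14,000/14.93 = 937.7. Under efficient mixed-model weighting, variable cluster size multiplies this by 1 − CV² × L(1 − L), where L = 14/(14 + 0.93) = 0.938. The factor is 0.963, and power is 94.7%, as stated. No baseline adjustment enters this calculation.

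**Where the planned estimator's variance lies.** For the unweighted estimator the design effect is (1 − ICC) + m(1 + CV²) × ICC = 0.93 + 200 × 1.64 × 0.07 = 0.93 + 22.96 = 23.89. The between-practice share is 22.96/23.89 = 96%. The unadjusted standard error is √[(0.258 × 0.742 + 0.188 × 0.812) × 23.89/14,000] = 0.0242, a 95% half-width of 4.75 percentage points.

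**Adding the practice's baseline proportion.** The between-practice part is multiplied by 1 − r², so the variance ratio is [0.93 + 22.96(1 − r²)]/23.89:

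| r (assumed) | variance ratio | reduction | 95% half-width (points) |
|---|---|---|---|
| 0 | 1.00 | 0% | 4.75 |
| 0.2 | 0.96 | 4% | 4.66 |
| 0.3 | 0.91 | 9% | 4.54 |
| 0.5 | 0.76 | 24% | 4.14 |
| 0.7 | 0.53 | 47% | 3.45 |

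Adding the individual baseline as well changes these ratios by less than 0.01.

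**Individual-level adjustment alone, as in the listed sensitivity models.** Under an independence model the single coefficient is roughly b = 0.07r + 0.93 × 0.3. The between-practice part is then multiplied by 1 − 2br + b², and the within-practice part by 1 − 2b × 0.3 + b². At r = 0, b = 0.279 and the variance ratio is 1.07, a small loss. At r = 0.3 it is 0.91, at r = 0.5 it is 0.79, and at r = 0.7 it is 0.66. It matches practice-level adjustment only near r = 0.3.

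**Simulation of the stated worry.** 140 practices, observed ICC about 0.07, CV 0.8, baseline suppressed by a different random amount in each practice, 500 runs per setting. With a true effect of −0.07, the mean estimate after practice-level adjustment was −0.069 to −0.071 and coverage 94–95%. The empirical standard error moved as follows:

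| latent practice correlation | observed practice correlation | unadjusted | practice-adjusted |
|---|---|---|---|
| 0 | 0.01 | 0.0224 | 0.0226 |
| 0.3 | 0.24 | 0.0231 | 0.0224 |
| 0.5 | 0.38 | 0.0224 | 0.0208 |
| 0.7 | 0.54 | 0.0226 | 0.0195 |

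The last three rows are variance reductions of 6%, 14% and 26%. Putting the observed correlations into the formula gives 6%, 14% and 28%. So r in the formula means the correlation that survives sampling noise and pandemic disturbance. In the one setting with no effect, the rejection rate was 6% with practice-level adjustment, 7% with individual-level adjustment and 8% unadjusted.

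**Availability.** Absence of a code counts as no event, so the primary outcome is said to "by definition, not have any missing data as the absence of a code describing an event or prescription is defined as the binary variable value" for no event. The same rule applied to the baseline year (an inference) gives a complete covariate for every analysed patient.

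**The case against.** The protocol never says that adjustment would bias the result. It pre-specifies a valid unadjusted analysis, explains the choice, considers an alternative baseline and keeps adjusted models as sensitivity analyses. The gain depends on a correlation that no document gives, and there are grounds to expect a weak one: disruption differed by date and region, new remote-consultation codes may have changed recording, and the outcome year starts 12 months after the baseline year ends. The full model is also left to the SAP.

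Much of this stands. The gain is uncertain and could be close to nil. The last argument does not rescue the choice, because the article itself fixes that the main analysis will not adjust for baseline. A weak covariate is a reason to expect little benefit, not a reason to leave it out when leaving it in costs almost nothing.

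Some stronger readings do not hold:

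- A reader might infer that the main analysis is biased. It is not; randomisation protects it with or without the covariate.
- A reader might infer that dropping adjustment undermines the stated 94.7% power. That figure reproduces with no baseline adjustment. The planned unweighted estimator gives about 82% on the same inputs, but that is a separate matter of weighting and does not arise from this change.
- A reader might take the sensitivity analyses to hold the more precise estimate. The two baseline-adjusted ones are described only at the individual level and could be slightly less precise than no adjustment if r is near zero.
- A reader might say that almost all outcome variance is between practices. The ICC puts it at 7%; the 96% refers to the sampling variance of the treatment-effect estimate.

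**Conclusion.** The point holds as an improvement available at almost no cost, not as an error. Uneven pandemic effects on baseline are no threat to validity. Leaving baseline out of the main model forgoes a possible gain in precision, and nothing in the stated reasons offsets that. The assumed range runs from no gain at r = 0, through 4–9% of the variance at r = 0.2–0.3, to 24% at r = 0.5 and 47% at r = 0.7; the lower part is quite possible given the pandemic. These figures rest on the protocol's ICC, cluster size and variation, and on the practice's baseline proportion being in the model. At zero correlation the simulation showed essentially no penalty. Because the data to be extracted already include this baseline, the choice should be settled while the analysts are still blind; it cannot credibly be revised afterwards.

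**What to change.** Before allocation codes are released, specify the primary model as arm, the stratification factors, individual unscheduled care (yes/no) in the 12 months before randomisation, the practice's proportion with unscheduled care in that same period, and a recruitment-period term with its cut points defined in advance. A baseline-by-period interaction is optional. State on which patients the practice proportion is computed; the analysed cohort needs no further extraction. Keep the participant-average risk difference as the target and the robust standard errors as planned. Retain the unadjusted model as a sensitivity analysis beside those already listed.

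The cost is a wording change in the protocol and SAP and a few extra model terms with 140 practices. No new data are needed, since the pre-randomisation year is already required for the first sensitivity analysis.

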### Stakeholder engagement

In addition to the multidisciplinary research team (academics, general practitioners (GPs), nurses, health psychologists, health economists), a Professional Advisory Group (led by SH) from members of the Primary Care Respiratory Society will meet regularly to offer advice on aspects of the IMP^2^ART implementation strategy, to contribute to raising the profile of the work, and to advise on longer-term sustainability. A Patient Advisory Group (led by TJ & NM) from the Asthma UK Centre Patient and Public Involvement (PPI) platform will be consulted regularly for their opinions on the development of the implementation components, research materials, interpretation of findings and dissemination.

### Internal pilot

The trial included an internal pilot completed between January 2021 and September 2021. The initial 12 practices were recruited as pilot practices with the aim of:Observing feasibility of the trial procedures (practice recruitment, initial data extraction, randomisation, mailing of the OPC quality improvement questionnaire, setting up the implementation strategy according to allocation).Exploring engagement with the IMP^2^ART implementation strategy (access to education modules, use of the patient-facing website, acceptability to the practice teams) and fidelity with which the components of the implementation strategy were adopted/adapted (video-recording of the facilitated IMP^2^ART workshops).

The trial processes for the 12 pilot practices proceeded as described for the main cluster-RCT (the remaining 132 practices), with the 12 practices randomised to either the implementation strategy or control. Process data from researcher and facilitator logs, and qualitative data from interviews with pilot practice staff were analysed to provide evidence for the funder’s progression criteria and inform the processes of the main trial. A number of minor adjustments were made to processes but no substantial changes were made to the implementation strategy or trial procedures [76].

### Ethical and governance considerations

The study has received ethical approval from NHS Lothian (REC No: 19/EM/0279), NRS and HRA approval (NRS Ref NRS/19/256672), and local governance as required in all areas. The decision of a practice to participate in the study is voluntary and will be based on a clear understanding of what is involved, detailed in an Organisational Information Document (OID) (Additional file 2). Practices will have sufficient time to consider the oral and written information provided, and to clarify points they do not understand. A practice may withdraw their consent to participate at any time.

The trial is overseen by an Independent Steering Committee, but a Data Monitoring and Ethics Committee is not appropriate as no outcome data will be available for monitoring until the end of the trial. No interim analysis is possible. The trial sponsor is the Academic and Clinical Central Office for Research and Development (ACCORD no: AC19081) who will assess risk and determine if an audit is required.

